### Health and lifestyle assessment

#### Baseline health

Baseline demographic and health characteristics of the study participants will include demographic characteristics, health record information (type of cancer, disease status, co-morbid conditions, cancer treatment received, side-effects of treatment) and information related to SCT (platelet and neutrophil engraftment, conditioning regimen received, toxicities due to conditioning regimen, documented infection, incidence of fever). These questionnaires will be filled out by the physician at baseline, 15, 30, 60, 85 and 180 days after stem cell infusion.

#### Dietary habits

Usual dietary intake will be assessed at four time points (baseline, 30, 85 and 180 days after infusion) using a 3-day dietary record [23]. Dietary records will be analyzed by a Registered Dietitian using Diet Analysis Plus 10.0 software (Thomson Wadsworth, Toronto, Canada). Participants and their parents will be instructed as to how to fill out these records by the research nurse.

#### Quality of life

Quality of life will be assessed using the Pediatric quality of life inventory (PedsQL) general and cancer module as a self-report, and PedsQL and Behavior Assessment System for Children (BASC-2) as parent proxy report. The PedsQL Measurement Model is a modular approach to measuring QOL in healthy children and adolescents and those with acute and chronic health conditions. The PedsQL Measurement Model integrates seamlessly both generic core scales and disease-specific modules into one measurement system. The 23-item PedsQL Generic Core Scales were designed to measure the core dimensions of health as delineated by the World Health Organization, including physical, emotional, social and school functioning. In addition, the cancer module will be assessed to provide greater measurement sensitivity. The reliability and validity of the PedsQL general and cancer module has been shown in pediatric cancer populations [24]. Participants will complete this measure.

The BASC-2 [25] is a standardized report measure of child behavior consisting of 150 items with self, parent proxy, or teacher report forms. The BASC yields scores for externalizing (i.e., hyperactivity, aggression, conduct problems) and internalizing (i.e. anxiety, depression, and summarization) behavior problems as well as for adaptive skills. Items are rated using a 4-point ordinal scale. Raw scores are converted into T scores. T-scores of 60 or greater are indicative of clinically significant behavior problems. Parents will be asked to complete this measure as a means of enhancing QOL measurement sensitivity.

#### Fatigue

Fatigue will be assessed using the multidimensional PedsQL fatigue scale. The recently developed 18-item PedsQL Multidimensional Fatigue Scale was designed to measure fatigue in pediatric patients and comprises the General Fatigue Scale (6 items), Sleep/Rest Fatigue Scale (6 items), and Cognitive Fatigue Scale (6 items). Reliability and validity of the pediatric multidimensional fatigue scale has been shown in cancer population [24]. Participants will complete this measure.

#### Objective measurements of physical activity

A triaxial accelerometer (Actual – Phillips respironics) will be used as an objective assessment of physical activity levels. Actual measures and records time-stamped acceleration in all directions, providing an index of physical activity intensity. The digitized values are summed over a user-specified interval of 1 min, resulting in a count value per minute (counts per minute). Accelerometer signals are also recorded as steps per minute. This gold standard measure provides a reliable and objective measure of physical activity levels, previously validated and tested for reliability [26,27].

The activity monitor (AM) will be put on when the participant gets up from bed each day and worn until the participant is ready to fall asleep. Participants can go about their normal, daily activities, including rigorous EX, swimming or bathing. Participants will be instructed to wear the activity monitor over their right hip on an elasticized belt for seven consecutive days. The AM can be worn over or under clothing. Additionally, participants will be asked to record, in a daily log, the time they put on and took off the monitor each day. This protocol and device was recently used in a study to asses physical activity among healthy Canadian children between 6-19 yr [28]. The research nurse will explain the instructions about how to use the AM and daily log at their first meeting.

### Health-related fitness assessments

The HRF assessments will be performed by a certified exercise physiologist. Participants will complete the assessments in the following order: resting blood pressure (BP), heart rate (HR) and electrocardiogram; body composition; musculoskeletal fitness (flexibility, muscular strength and endurance); functional mobility test and cardiorespiratory fitness. Adequate recovery and hydration will be provided, with the total fitness assessment time approximately 2.0 hours.

#### Submaximal aerobic test

Resting HR will be measured using a heart rate monitor (Polar Electro RS300X, Finland) and resting BP (mmHg) will be measured following the Fourth Report published by the U.S. Department of Health and Human Services [29]. All participants will perform a submaximal EX test on a treadmill. A modified protocol suggested by Bar-Or (1993) adjusted by height will be used. The initial velocity of the test will be determined upon child height (Table 1) based on Bar-Or suggestion for healthy kids maximal testing [30]. All participants will start the test with an upgrade of 5%. Every 2 minutes (Tanner stages I-IV) and every 3 minutes (Tanner stage V), the slopes will increase 2.5% until 80% of age-predicted maximal HR is achieved. Age-predicted maximal HR will be calculated using the equation 208- (0.7× age) [31].

**Table 1 T1:** Sub maximal aerobic test; setting speed according to height of each participant

**STATURE****(****cm)**	**SPEED (km/h)**
≤ 109.9 cm	3 km/h
110–129.9 cm	4 km/h
≥ 130 cm	4.8 km/h

All the children will be verbally encouraged during the test. Gas-exchange data will be measured in a mixed metabolic cart (True One Metabolic Cart, ParVo Medics Inc, Utah, U.S.) and specific pediatric face-masks (Hans Rudolph Model 8930, 8940, 8950, 8960). The duration of the test, the maximal load reached (velocity and slope), and the maximal distance walked will be recorded. In addition, parameters including ventilation (VE), ventilatory equivalent of carbon dioxide (VCO_2_), respiratory exchange ratio (RER), and Respiratory Quotient (RQ) will be recorded.

Oxygen uptake and HR will be determined at Ventilatory threshold (VT). VT will be determined using the criteria of an increase in both the ventilatory equivalent of oxygen (VE . VCO_2_^-1^) and end-tidal pressure of oxygen (PetO_2_) with no increase in the VCO_2_ while RER remained below 1.0 [32]. All the EX tests will be performed under similar environmental conditions and at the same time of the day (10:00 am – 13:00 pm). Participants will be directed to consume their usual breakfast 3 hours prior to the testing.

Previous familiarization sessions will not be possible due to the nature of the study population (i.e., approximately ½ of participants will be from outside of Calgary). To diminish the anxiety and fear that fitness tests may generate, participants and parents will have the opportunity to watch a video explaining and showing all assessments.

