### Study population

A total of 24 children will be recruited for this RCT; 12 patients will be assigned to an EX training program and 12 subjects will be assigned to a control group (without any specific training). A sequence to allocate participants randomly will be generated by the software Research Randomizer, a research tool provided by the Social Psychology Network (http://www.socialpsychology.org). Allocation concealment will be ensured. After baseline assessments each participant will choose a sealed, non transparent envelop, which contains a number that will allocate the subjects to the control or EX group. The research coordinator will be responsible for the random allocation.

Eligibility criteria includes: (1) autologous SCT at Alberta Children’s Hospital (ACH) for malignancy, (2) age 5 to 18 years of age, (3) will be receiving myeloablative conditioning regimen, (4) no evidence of cardiac or pulmonary failure associated with treatment (shortening fraction (SF) ≥28%, ejection fraction (EF) ≥ 50%), (5) no functional nor cognitive limitation that would prohibit performance of the home-based training, (6) approval by treating oncologist for participants, (7) a parent or legal guardian must sign the consent form, and (8) children should express verbal assent to participate. The entire team of assessors and the persons performing the statistical analyses will be blinded to group assignment.

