### EX intervention 

This RCT will be a biphasic EX intervention.

Phase 1 – The inpatient phase will be performed at the ACH during conditioning and the isolated phase of autologous SCT.

Phase 2 – The outpatient phase will take place after discharge. The participants will participate in a 10 week mixed supervised and home-based EX program utilizing the Wii device.

In both phases participants will wear a portable heart rate monitor (RS300X Polar) when at the EX sessions to ensure safety and target the aerobic EX intensity between 50% and 70% of heart rate reserve (HRR), depending on the physical status of each child.

The training session will be cancelled if the child has platelet levels below 10.000/ μl, hemoglobin levels below 8 g/dl, fever greater than 38°C, pain, diarrhea, hemorrhage or any other complication(s) the oncologist thinks may worsen with EX. Additionally, a session may be cancelled if the child doesn’t want to participate.

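### The treadmill test stops at a fixed heart rate whether or not the ventilatory threshold has appeared, so the threshold outcomes are unobservable in an unknown share of children, and that loss depends on the value being measured

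*Protocol article*

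**What the plan says.** All of this is in the Protocol article.

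- **Stop rule** (Submaximal aerobic test): "the slopes will increase 2.5% until 80% of age-predicted maximal HR is achieved". The maximum is predicted from age: "Age-predicted maximal HR will be calculated using the equation 208- (0.7× age" (closing bracket omitted).
- **Threshold outcomes** (same section): "Oxygen uptake and HR will be determined at Ventilatory threshold (VT" (closing bracket omitted). The threshold is recognised by a rise in a ventilatory equivalent and in end-tidal oxygen pressure, "with no increase in the VCO_2_ while RER remained below 1.0".
- **Other outputs of the test** (same section): "The duration of the test, the maximal load reached (velocity and slope), and the maximal distance walked will be recorded". Ventilation and gas-exchange variables are recorded too. Resting heart rate is measured, but no value is quoted.
- **Training intensity** (EX intervention): sessions are to "target the aerobic EX intensity between 50% and 70% of heart rate reserve (HRR), depending on the physical status of each child".
- **Status and analysis**: physical fitness belongs to the secondary objective. Data analysis plans doubly multivariate repeated measures ANOVA for the primary and secondary objectives. There are to be 12 children per arm (Study population), with the age criterion "age 5 to 18 years of age".

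**The concern.** The test ends on heart rate alone, while two of its outcomes exist only if a respiratory event occurs before that heart rate is reached. The criterion is a rise in two signals, so some data beyond the threshold are needed to recognise it. The usable ceiling is therefore somewhat below the stop itself.

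This is not ordinary missing data. Whether VT is seen depends on where VT lies, which is the quantity to be compared between arms. Repeated measures ANOVA ordinarily drops a child with any missing value among the variables and visits analysed together. The comparison would then be confined to children whose threshold came early enough at every visit, and randomisation does not protect a comparison selected in that way. With 12 children per arm, a few losses already matter.

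This concerns the stopping point only. How the VT criterion is worded is a separate matter.

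**Working it through.** **Inputs from the article.** Predicted maximum M = 208 − 0.7 × age; stop S = 0.8 × M; top of the training zone T = R + 0.7 × (M − R), where R is resting heart rate; ages 5 to 18. The article states no figure for the share of children reaching VT, so there is none to reproduce.

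**Step 1: the ceiling on an observable heart rate at VT.**
- Age 5: M = 208 − 3.5 = 204.5; S = 163.6 bpm.
- Age 12: M = 208 − 8.4 = 199.6; S = 159.7 bpm.
- Age 18: M = 208 − 12.6 = 195.4; S = 156.3 bpm.

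No child can record a heart rate at VT above these values. This needs no outside data.

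**Step 2: where the stop sits on the heart-rate-reserve (HRR) scale (context only).** Setting S = T gives 0.8M = 0.7M + 0.3R, so R = M/3: 68.2 bpm at age 5, 66.5 at age 12 and 65.1 at age 18. Above that resting rate the stop lies below 70% HRR. In general the stop is at (0.8M − R)/(M − R). At age 12, over an assumed range of R:

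| Resting HR (assumed) | Zone top T (bpm) | Stop S (bpm) | Stop as % HRR |
|---|---|---|---|
| 60 | 157.7 | 159.7 | 71.4 |
| 70 | 160.7 | 159.7 | 69.2 |
| 80 | 163.7 | 159.7 | 66.6 |
| 90 | 166.7 | 159.7 | 63.6 |
| 100 | 169.7 | 159.7 | 59.9 |

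For resting rates of 70 to 100 the gap is 1 to 10 bpm. At 60 the order reverses. The share of children above break-even also rests on assumption. With normally distributed resting rates (SD 10 to 12) and ages 5 to 18, it is 38–50% at a mean of 65 bpm, 56–69% at 70 and 84–93% at 80.

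**Step 3: the share with VT not reached (illustration).** Assume VT is normally distributed on the HRR scale with SD 8 percentage points. At age 11.5, M = 199.95 and S = 159.96. The share not reached is the probability that VT exceeds the stop:

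| Resting HR | Stop (% HRR) | Mean VT 55% | 60% | 65% | 70% |
|---|---|---|---|---|---|
| 70 | 69.2 | 4% | 12% | 30% | 54% |
| 80 | 66.7 | 7% | 20% | 42% | 66% |
| 90 | 63.6 | 14% | 33% | 57% | 79% |
| 100 | 60.0 | 27% | 50% | 73% | 89% |

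Out of 24 children at one visit, that is about 1 (0.04 × 24 = 0.96) to about 21 (0.89 × 24 = 21.4). The mean, the SD and the resting rates are all assumptions.

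**Step 4: direction of bias.** Two mechanisms pull apart. If training raises the heart rate at which VT occurs, the fitter children are lost. If resting heart rate is high, the stop falls at a lower % HRR (step 2), so children with high resting rates, possibly the less fit, are lost first. The article gives nothing from which to weigh one against the other.

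**The case against.** The strongest reply has four parts.

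1. **The training zone does not locate VT.** A reader might infer from step 2 that, because the stop is often below the training ceiling, VT will often be missed. That does not follow. The 50–70% range is an exercise prescription, and no section links it to VT. At resting rates of 70 to 100 the stop still falls at about 60–69% HRR, in the upper half of that zone. This objection stands in full.
2. **VT is not the only aerobic outcome.** Duration, load and distance are recorded and do not need VT, and nothing ranks VT above them. This stands. It limits the damage to the two VT variables and supplies the remedy.
3. **The bias is not shown to run towards no effect.** A reader might suppose that the exercise arm loses its best values. Because the stop is set by heart rate and not by workload, a VT that comes at a higher load need not come at a higher heart rate. This stands; see step 4.
4. **Coding of an unreached VT, and the ranking of fitness outcomes, may sit in a full protocol or SAP that is not shown.** This is fair, and silence on coding is not the finding. But no later document can recover a threshold that the test was stopped too early to show. The article itself fixes both the stop and the outcome.

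**Conclusion.** The point holds as a minor one. By the article's own rules VT is unobservable in any child whose threshold lies above 80% of predicted maximal heart rate, and the loss is related to the value measured. A complete-case repeated measures ANOVA of oxygen uptake or heart rate at VT may therefore be biased, in an unsettled direction.

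The size cannot be fixed from the document. The range of about 4% to 89% not reached rests on an assumed mean VT of 55–70% HRR, SD 8 points, resting heart rate of 70–100 bpm and age 11.5. It shows that the article gives no basis for expecting the outcome to be measurable; it does not show that VT will usually be missed. That the stop lies below the training ceiling for most children likewise depends on a mean resting rate of about 70 bpm or more, which the article does not state.

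The primary immune outcome is untouched, as are the other fitness tests and the remaining outputs of this one.

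**What to change.** Leave the stop rule as it is, and reconcile the statements on stopping and on VT as follows.

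- Name time to 80% of predicted maximal heart rate (the recorded test duration), or the load reached there, as the aerobic fitness endpoint for the secondary objective. Every child who completes the test to the stop yields it. For a child who ends earlier for another reason, record the time and the reason.
- Analyse that endpoint relative to the child's own baseline, since treadmill speed depends on height and stage length on Tanner stage.
- Optionally add heart rate and oxygen uptake at an early stage that every child completes. A later common stage will not do: a deconditioned child could reach the stop before it, which brings back fitness-related loss.
- Keep VT as supportive. Record *not reached by 80% of predicted maximal heart rate* as a result in its own right, analyse it as censored at the stop, and report the number not reached by arm and visit.

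The cost is wording and a modest change of analysis for VT. Test duration, load, heart rate and gas exchange are already collected, so no procedure is added. The drawback is that VT becomes a supportive outcome.

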#### Functional mobility test

This test is used to measure the capacity of the children to perform daily activities. We will perform the timed up and go test (TUG) in 3 m [33,34]. For the TUG, the child is sitting with 90° hip and knee flexion and at a given signal the child will get up, walk 3 m, turn and come back as fast as possible without running. The researcher measures the time spent performing this test. The test will be performed three times and the best time will be registered. Between each attempt the child will rest for 2 minutes.

#### Musculoskeletal fitness

##### Muscular endurance

Muscular endurance is described as the ability of a muscle or a muscle group, to generate force repeatedly or for an extended period of time. Muscular endurance can be determined by measuring the number of repetitions or time to fatigue. We are going to ask the children to perform three tests: (a) partial curl-up, (b) modified push-up and (c) sit and stand test.

a) Partial curl-up will assess the muscular endurance of the abdominal muscles. The FITNESSGRAM protocol will be used [35]

b) Modified push-up: This test measures the endurance of upper body muscles.

The modified push-up will require the participant to start with hands shoulder-width apart with the elbows and body straight. The knees will be flexed 90° and the ankles crossed. The test consists of doing as many repetitions as possible continuously until failure. To ensure the participant is properly completing the push up, they will have to lower their torso until they come into contact with a foam roller (10 cm diameter) on the ground (rather than a fist).

c) Squat test: Will assess the muscular endurance of the lower body. The participant stands in front of a chair, facing away from it, with their feet shoulder width apart. The participant squats down lightly touching the chair (located at 90 ˚ hip flexion) with their backside before standing back up and repeats this sequence of movements for 30 seconds [36]. The assistant counts and records the number of successfully completed squats.

##### Strength assessment

Strength is defined as the maximal force or torque developed by a muscle, or a muscle group. Maximum isometric contraction values will be done by assessing (a) knee extension and (b) grip strength.

a) Knee extension will be performed by using the “break” technique, in which the examiner gradually overcomes the muscle force and stops at the moment the extremity gives away [37,38]. All tests will be performed with the tested limb segment in a position that will be not affected by gravity. The tester will manually stabilize the body part proximal to the tested limb segment during testing. Before the test, the assessor will demonstrate to the patient the muscle contraction. The piston of the dynamometer will be held perpendicular to the anterior surface of leg. The plate of the dynamometer will be placed just proximal to the ankle on the anterior surface of the leg. The subject will be seated on the edge of a padded mat table with the knee flexed 90°. Measures of strength of the right and left sides will be assessed. A sum will be determined in kilograms from the best score of 2 trials recorded for each muscle group.

b) Grip strength will also be assessed using a hand-dynamometer (Baseline®). Measures of strength of the right and left sides will be assessed. A sum will be determined in kilograms from the best score of 2 trials recorded for each muscle group, according to the CPAFLA protocol [39].

#### Flexibility

Sit and reach test measures the flexibility of the hamstrings and lower back muscles [39]. CPAFLA protocol will be followed [39].

#### Body composition

Standing height and body mass will be measured. We will measure standing height to the nearest 0.1 cm with a clinical stadiometer (SECA, Birmingham, UK), while children stand barefoot. Body mass will be measured to the nearest 0.01 kg using a balance scale (Health o Meter, Illinois, US) with the subjects in their underwear and will calculate body mass index (BMI) as weight height [mass (kg)/height (m^2^)]. Estimated children’s fat-free mass (FFM) will be calculated from the following equation (1): FFM = body mass – fat mass (FM), where FM = 4.95 x Body density (BD) x body mass. Children’s BD will be estimated from skin fold thickness at the triceps, biceps, sub scapular, and suprailiac area. In all subjects, each skin fold will be obtained in duplicate by the same researcher using standard equipment (Harpender skin fold caliper, Bath international, UK) and the mean value per skin fold utilized for statistical analysis [39]. A third skin fold measure will be taken if the difference between the first two measures is greater than 4 mm. Different equations depending on children’s age and gender will be used to calculated BD (1) BD = 1,169 - 0,0788 * log Σ 4 skin folds and BD = 1,2063 - 0,0999 * log Σ 4 skin folds (for boys and girls, respectively, aged ≤12 yr) and (2) BD = 1,1533 - 0,0643 * log Σ 4 skin folds and BD = 1,1369 - 0,0598 * log Σ 4 skin folds (for boys and girls, respectively, aged ≥ 13 yr) [40].

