Systematic reviews support the promising role of EX as a safe and effective intervention to improve HRF and quality of life and fatigue outcomes in children with cancer [3,4]. However, most of the research was performed in children with ALL. Only three articles have been published showing the effect of an EX intervention in children undergoing SCT and the outcomes are promising including improve in cardio respiratory capacity, strength, fatigue and QOL [7,14,15]. This study will provide details about the effect of an EX program on fatigue and QOL as a self-report outcome and also will be compared with parent’s proxy report.

3. The effects of an EX intervention on body composition

The aim of this study is to determine if an early EX intervention during SCT will (a) avoid loss of body weight. Survivors of pediatric patients who went undergoing a SCT are at an increased risk to have less lean mass and an excess of fat mass compared with healthy peers [49].

Given the scarcity of literature on the effect of an EX program on the immune system recovery, QOL, physical activity levels and HRF measures for pediatric cancer patients undergoing SCT, the SCORE study will generate new knowledge and be instrumental in developing future clinical and community-based programming for this population. This will be the largest known study in children undergoing autologous SCT and will provide us with valuable information for a future multisite study. This research could add biologic plausibility to the association between EX and immune system recovery after autologous SCT that may identify new targets for interventions, and inform clinical recommendations for improving survival. Ultimately, this project will enable us to achieve more effective targeted interventions that help pediatric cancer patients achieve healthy levels of PA and HRF and with the hope of optimizing disease and treatment related outcomes.

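### The printed fat-mass formula is unusable: it gives a fat mass about five times body weight and a negative fat-free mass for every child

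*Protocol article*

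**What the plan says.** The Body composition section of the protocol article derives fat-free mass (FFM) from fat mass (FM), and FM from body density (BD): "FFM = body mass – fat mass (FM), where FM = 4.95 x Body density (BD) x body mass".

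On the source of BD it says: "Children’s BD will be estimated from skin fold thickness at the triceps, biceps, sub scapular, and suprailiac area". It then gives four equations, with decimal commas:

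- boys and girls aged 12 or under: "BD = 1,169 - 0,0788 * log Σ 4 skin folds and BD = 1,2063 - 0,0999 * log Σ 4 skin folds"
- boys and girls aged 13 or over: "BD = 1,1533 - 0,0643 * log Σ 4 skin folds and BD = 1,1369 - 0,0598 * log Σ 4 skin folds"

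The base of the logarithm is not stated. No other section of the article converts density to fat.

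Body composition is among the outcomes listed in the Abstract and is the third research theme in the Discussion. The background given for that theme is that survivors of transplantation "are at an increased risk to have less lean mass and an excess of fat mass compared with healthy peers". That sentence shows why fat and lean mass matter to the trial; it does not use or repeat the formula.

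**The concern.** FFM is defined as body mass minus FM, so FM must lie between zero and body mass. Body density is close to 1, and a multiplier of 4.95 then puts FM at roughly five times body mass. The slope also looks wrong. All four density equations fall as the skinfold sum rises, but printed FM rises with density, so at a given weight a fatter child receives a smaller FM.

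FM and FFM are the only fat and lean measures that the section derives. If they are coded as printed, the trial has no usable measure of either, and a later multisite study, which the Discussion hopes for, could inherit the formula.

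**Working it through.** The article prints no numerical FM or FFM, so there is no stated figure to reproduce. The check evaluates the printed formula with the printed density equations.

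**Inputs from the Body composition section.** With S the sum of four skinfolds (mm) and M body mass (kg):

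- BD = 1.169 - 0.0788 log S (boys, 12 or under)
- BD = 1.2063 - 0.0999 log S (girls, 12 or under)
- BD = 1.1533 - 0.0643 log S (boys, 13 or over)
- BD = 1.1369 - 0.0598 log S (girls, 13 or over)
- FM = 4.95 × BD × M; FFM = M - FM

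**Assumptions, not in the article.** S from 20 to 80 mm, widened to 15 to 120 mm; base-10 log, with natural log as an alternative; illustrative body masses of 30 and 40 kg.

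**Step 1: level (base-10 log).**

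| Equation | BD at 20 mm | FM/M at 20 mm | BD at 80 mm | FM/M at 80 mm |
|---|---|---|---|---|
| Boys, 12 or under | 1.0665 | 5.28 | 1.0190 | 5.04 |
| Girls, 12 or under | 1.0763 | 5.33 | 1.0162 | 5.03 |
| Boys, 13 or over | 1.0696 | 5.30 | 1.0309 | 5.10 |
| Girls, 13 or over | 1.0591 | 5.24 | 1.0231 | 5.06 |

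FM is 5.03 to 5.33 times body mass, so FFM is -4.03 to -4.33 times body mass.

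Worked case, boy aged 12 or under, M = 30, S = 30: BD = 1.169 - 0.0788 × 1.4771 = 1.0526; FM = 4.95 × 1.0526 × 30 = 156.3 kg; FFM = 30 - 156.3 = -126.3 kg.

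**Step 2: does the result depend on the assumptions?** Over 15 to 120 mm, FM/M is 4.94 to 5.39 with base-10 logs and 3.60 to 4.85 with natural logs. FFM is negative throughout. For FFM to reach zero, BD must fall to 1/4.95 = 0.202. The equation that gets there soonest (girls, 12 or under) needs log S = (1.2063 - 0.202)/0.0999 = 10.05. That is a skinfold sum above 10^10 mm with base-10 logs, or about 23,000 mm with natural logs.

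**Step 3: response to skinfolds at fixed weight.** Same boy at 30 kg, S rising from 30 to 50 mm: BD falls from 1.0526 to 1.0351, and printed FM falls from 156.3 to 4.95 × 1.0351 × 30 = 153.7 kg. The direction is wrong.

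**Step 4: response when weight also changes.** Between 30 and 50 mm, BD falls by only 1.7%, so a gain of more than about 0.5 kg (30 × 1.0526/1.0351 = 30.5) makes printed FM rise. From 30 kg and 30 mm to 32.4 kg and 50 mm, printed FM goes up from 156.3 to 4.95 × 1.0351 × 32.4 = 166.0 kg.

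Printed FFM is about -4 times weight. Over the same skinfold change it falls once the gain exceeds about 0.6 kg (126.3/4.124 = 30.6). In a boy whose weight rises while his skinfolds fall, from 40 kg and 40 mm to 42 kg and 30 mm, printed FFM drops from -166.5 to -176.8 kg, although that pattern points to lean gain.

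**Step 5: is it only a wrong operator?** Replacing multiplication by division gives FM/M = 4.95/BD. With base-10 logs over 15 to 120 mm this is still about 4.5 to 5.0, so a term is missing as well. A form such as FM = (4.95/BD - 4.5) × M gives 6.1 kg at 30 mm and 8.5 kg at 50 mm for the 30 kg boy. Those values are plausible and move the right way, but the division and the constant 4.5 are assumptions that do not appear in the article.

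**The case against.** The level error has no answer in the article. The case on the other side concerns its reach.

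- **Direction.** A reader might infer that the sign of any exercise effect on FM and FFM is reversed, or that every child who gains fat would be recorded as losing it. The document's equations do not support that. The reversal of FM is exact only at fixed body mass; step 4 shows printed FM rising when weight and skinfolds rise together. What stands is that FM mostly follows weight and FFM mostly moves against it.
- **Importance.** FM and FFM are derived, non-primary variables. The primary objective is immune cell recovery, the sample size rests on natural killer cell activity, and the secondary objective names fitness, activity and quality of life. The one aim spelled out under the body composition theme concerns loss of body weight, which is measured directly. This limits the damage but does not make the formula usable.
- **Misprint.** The line may be a publication slip: the BMI definition in the same section also seems to lack an operator. Values such as 156 kg of fat in a 30 kg child would probably be noticed, and FM can be recomputed from stored data. This is fair mitigation, but no other part of the article supplies a correct version.
- **Condensed article.** An article may leave detail to a fuller protocol. Here, though, an explicit derivation is printed and is wrong; the point is not about an omission.

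**Conclusion.** The concern holds for the formula as printed. With the section's own density equations, FM is 5.03 to 5.33 times body mass over 20 to 80 mm with base-10 logs, and FFM is negative for every child under either log base and at any realistic skinfold sum. At fixed weight, FM responds to skinfolds in the wrong direction; otherwise it is driven mainly by weight. Neither variable can be used to describe fat or lean mass.

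The skinfold range and body masses are illustrative, and the conclusion does not depend on them. It also does not depend on which replacement formula is right. The effect is confined to derived FM and FFM.

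**What to change.** 1. Correct the density-to-fat conversion against the source from which the protocol took it, and cite that source beside the formula. The form in step 5 is a candidate to confirm, not something the article states.
2. Keep FFM as body mass minus FM.
3. State the base of the logarithm in the four density equations.
4. Add to the derivation program a check that FM is above zero and below body mass.
5. Recompute any FM or FFM values already derived.

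The cost is a one-line correction to the formula, a stated log base and one range check. The inputs are body mass and the four skinfolds, already planned, so no measurement or visit changes.
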